### 2.8. Outcome measures

#### 2.8.1. Early efficacy evaluation 3 days after the first dose of the study drug.

The efficacy evaluation 3 days after the first dose of the study drug will result in the following categorizations: effective (in addition to improvements in 1 or more clinical symptoms there will be improvements to pneumonia images or inflammatory findings; WBC < 9000/ mm^3^ or a decrease from the highest CRP level), no effect, or indeterminable (lack of evaluation information or evaluation items worsening due to causes other than pneumonia).

#### 2.8.2. Efficacy evaluation at the time of EOT.

The efficacy evaluation at the time of EOT will result in the following categorizations: effective (in addition to improvements in 1 or more clinical symptoms accompanied by resolution of fever, there will be improvements to pneumonia images or inflammatory findings; WBC < 9000/ mm^3^ or a decrease from the highest CRP level), ineffective, or indeterminable (lack of evaluation information or evaluation items worsening due to causes other than pneumonia).

#### 2.8.3. Efficacy evaluation at the time of TOC.

TOC will be determined 5 to 10 days after the last dose of the study drug, with subjects classified as being cured, not cured, or indeterminable (lack of evaluation information, evaluation items worsening due to causes other than pneumonia, or clinical symptoms or inflammatory findings improved but the antibacterial drug was prescribed for reasons other than NHCAP before the time of TOC). Cured satisfies all the following criteria: treatment determined to be effective at the time of EOT; or an additional prescription of an antibacterial drug is not necessary after the EOT to the TOC; body temperature, WBC count, CRP level did not deteriorate after EOT, and resulting in an additional prescription of an antibacterial drug not being required; improved symptoms compared to the EOT; and improved chest X-ray compared to the EOT.

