### 2.12. Statistical analysis

The target population in safety analyses (SAS) was defines as patients registered as study participants and administered the study drug at least once during the study period. The target population of the full analysis set (FAS) was defined as a subset of SAS consist of patients who are able to be evaluated whether “cured” or “not cured” at TOC. The modified FAS was defined as an extension of the FAS that includes patients who are able to be evaluated whether “cured” or “not cured” at the TOC or at the withdrawal from the protocol treatment. The target population in the per protocol set analysis was defined as patients with adherence of equal or higher than 80% to the protocol treatment (doses of the study drug).

The objective of the primary analysis is to obtain the lower limit of the 95% CI of the binomial probability of frequency of “cured.” The Clopper–Pearson method was planned to be used here. The FAS was planned as the target population.

A sensitivity analysis for the primary analysis is planned to evaluate the upward bias in the estimation of the probability of the treatment success, that will be introduced by the exclusion of cases who are withdrawn from the protocol treatment before TOC evaluation, obtained from the primary analysis. Aiming this, the modified FAS was set as the target population of the sensitivity analysis and the 95% CI of the binomial probability was planned to be calculated via the Clopper–Pearson method.

The planned analyses on the secondary endpoints are same with the primary analysis; the 95% CI of the binomial probability but the target population, that was set on the FAS.

Associations of the patients background and the primary/ secondary endpoints were planned to be analyzed exploratorily. The patients background was defined as the results from evaluations on respective patients at the visits for the first administration, or before the date, during the patient’s study period.

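### Whether a patient given an antibacterial for a non-NHCAP reason leaves the primary analysis depends on whether the patient improved, and the planned sensitivity analysis does not show the effect

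*Protocol article*

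**What the plan says.** Section 2.8.3 of the protocol article sorts patients at TOC into cured, not cured and indeterminable. There are three routes to indeterminable. Two do not depend on improvement: "lack of evaluation information, evaluation items worsening due to causes other than pneumonia". The third does: "clinical symptoms or inflammatory findings improved but the antibacterial drug was prescribed for reasons other than NHCAP before the time of TOC".

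Cured requires a list of criteria that ends with "improved symptoms compared to the EOT; and improved chest X-ray compared to the EOT".

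Section 2.12 defines the FAS as "a subset of SAS consist of patients who are able to be evaluated whether “cured” or “not cured” at TOC". For the primary analysis, a Clopper-Pearson 95% interval for the proportion cured, it states: "The FAS was planned as the target population". The one sensitivity analysis described uses the modified FAS, which takes in "patients who are able to be evaluated whether “cured” or “not cured” at the TOC or at the withdrawal from the protocol treatment". Its stated purpose is to examine upward bias from leaving out patients withdrawn before TOC.

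**The concern.** Two patients may receive the same unrelated antibacterial before TOC and be treated differently because of how their pneumonia went. If symptoms or inflammatory findings improved, the patient leaves the denominator. If neither improved, the patient usually stays as a failure. Selection into the primary population then depends on the outcome being estimated.

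The trigger is also wider than the cure rule. It needs improvement in symptoms or in inflammatory findings, whereas cure needs every criterion, including the chest X-ray. A patient with a falling CRP but no X-ray improvement is not cured, yet leaves the FAS once the prescription is attributed to a reason other than NHCAP. The study is open-label, so that attribution is made with treatment known.

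At stake are the single-arm cure rate and its lower confidence limit, the trial's primary quantity. Section 2.11 allows for 30% indeterminable, so the rules behind that category shape the denominator.

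**Working it through.** **How recipients of a non-NHCAP antibacterial are classified (2.8.3 with 2.12)**

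| Course without regard to the other prescription | Status at TOC | In FAS? |
|---|---|---|
| Meets all cure criteria | Indeterminable (symptoms improved, so the clause applies) | No |
| Fails the cure rule, but symptoms or inflammatory findings improved | Indeterminable | No |
| Neither improved; not explained by missing data or a non-pneumonia cause | Not cured | Yes, as failure |
| Neither improved; information lacking, or worsening due to another cause | Indeterminable by another route | No |

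The first row removes cures and pulls the FAS rate down. The second removes failures and pushes it up. The net direction depends on who receives the drug.

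**Inputs**
- True cure rate p = 0.875, the planning value in 2.11. I assume that the other drug does not change the pneumonia outcome.
- Overall share r receiving a non-NHCAP antibacterial before TOC. The article does not give it, so I assume 5, 10 and 20%.
- Evaluable patients before the clause acts: 77 × 0.70 = 53.9, taken as 54. The article has no figure of its own for this point. As a check on the 77: reading 2.11 as a half-width below 0.10, with cures rounded down, gives 53 evaluable and 53/0.70 = 75.7, so 76. That is close to 77, and nothing below depends on it.

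**Scenario 1: receipt independent of outcome, no failure partly improves.** All cures among recipients leave and all failures stay.

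FAS rate = p(1 − r) / [p(1 − r) + (1 − p)]
- r = 5%: 0.83125/0.95625 = 0.869
- r = 10%: 0.7875/0.9125 = 0.863
- r = 20%: 0.7000/0.8250 = 0.848

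This is 0.6, 1.2 and 2.7 points low. Starting from 54 patients and using expected (non-integer) counts, the Clopper-Pearson lower limit falls from 0.757 to 0.746, 0.735 and 0.709. Part of that fall comes from the smaller denominator.

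**Scenario 2: failures receive the drug three times as often as cures, and all of them partly improve.** All recipients leave. With receipt q in cures and 3q in failures, r = 0.875q + 0.125(3q) = 1.25q, so q = 4, 8 and 16%.

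FAS rate = p(1 − q) / [p(1 − q) + (1 − p)(1 − 3q)]
- r = 5%: 0.840/(0.840 + 0.110) = 0.884
- r = 10%: 0.805/(0.805 + 0.095) = 0.894
- r = 20%: 0.735/(0.735 + 0.065) = 0.919

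This is 0.9, 1.9 and 4.4 points high.

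**Does the modified FAS reveal this?** It adds patients who could be rated at withdrawal. A recipient who completed treatment and was set aside at TOC under the antibacterial clause is in neither set.

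**Would deleting the improvement condition help?** Every recipient would then leave.
- Scenario 2 is unchanged, because all recipients leave already.
- Suppose 10% of cures and 30% of failures receive the drug (12.5% overall) and no failure partly improves. The present rule gives 0.7875/(0.7875 + 0.125) = 0.863, which is 1.2 points low. With the condition deleted, the rate is 0.7875/(0.7875 + 0.125 × 0.70) = 0.7875/0.875 = 0.900, which is 2.5 points high.

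Deletion can therefore replace a small downward bias with a larger upward one.

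**The case against.** The strongest defence is that the asymmetry is deliberate. A cure that follows a second antibacterial cannot be credited cleanly to lascufloxacin, while a failure despite extra treatment is still a failure. Keeping such failures is the cautious choice in an uncontrolled study. This stands as a reason to leave the clause in the primary analysis. It does not cover the partial improvers: the clause also removes patients who fail the cure rule, and that is not cautious.

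A reader might infer that every non-improving recipient is forced in as a failure, that no recipient can ever count as cured, and that the cure rate is therefore biased downward. The text does not go that far. Worsening from a cause other than pneumonia is a separate route out, and it may well apply to a patient with another infection. No precedence between cured and indeterminable is written, and the cure criteria speak of a further antibacterial not being needed, so a patient could literally meet both definitions. The specific clause is the natural one to apply. If cured took precedence instead, the clause would remove only partial improvers who failed, and the bias would be upward.

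It is also fair to say that the article gives no frequency, that the effect at 5% receipt is under one point, and that a full protocol or analysis plan, not shown, may contain further sensitivity analyses. If it does, the second half of this point is answered. The outcome-dependent rule itself is stated expressly in the article.

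**Conclusion.** The point holds in a limited form. On the natural reading of 2.8.3 and 2.12, membership of the primary population among recipients of a non-NHCAP antibacterial depends on their outcome, and the sensitivity analysis described does not show the consequence.

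Neither the direction nor the size can be fixed from the article. At a true cure rate of 0.875 and 5 to 20% overall receipt, the two scenarios run from 2.7 points low to 4.4 points high. These rest on assumed receipt, an assumed threefold ratio in the second scenario, and no effect of the other drug on the pneumonia. They illustrate the possible effect and do not predict it. If such prescriptions are rare, the effect is small.

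The documents support neither a claim of systematic downward bias nor deletion of the improvement condition.

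**What to change.** Leave the clause in 2.8.3 as it is for the primary analysis. In 2.12, add two Clopper-Pearson 95% intervals for the primary endpoint. Each puts back into the denominator every patient made indeterminable by the antibacterial clause:

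- (a) rated cured or not cured on the observed clinical criteria, regardless of the other prescription;
- (b) all counted as not cured.

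Under the assumptions above, (a) returns 0.875 in both scenarios. Interval (b) centres on p(1 − r) = 0.831, 0.788 and 0.700 in scenario 1, and on p(1 − q) = 0.840, 0.805 and 0.735 in scenario 2. The spread between (a), (b) and the primary result shows how far the lower limit depends on the clause.

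The cost is two extra intervals from assessments already scheduled. Each has a limit. Interval (a) credits lascufloxacin with any benefit of the other drug. Interval (b) is conservative, because it scores some improved patients treated for an unrelated infection as failures. No treatment, visit or data item changes.

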### 2.5. Exclusion criteria

The exclusion criteria are as follows:

(1)Patients with a previous history of hypersensitivity or serious adverse reaction to quinolones.(2)Patients with complications or a past history of a convulsive disorder, such as epilepsy.(3)Female patients who are pregnant or may be pregnant.(4)Patients with severe dysfunction in the liver or heart.(5)Patients with severe or progressive underlying disease or complication (patients with diabetes with HbA1c > 8.0% regardless of treatment, patients with advanced cancer whose prognosis cannot be expected during the observation period, patients with advanced cancer requiring surgery, etc).(6)White blood cell count ≤ 2000/ mm^3^ at the medical facility.(7)Patients with a severe infection requiring treatment with intravenous antibacterials or mechanical ventilation.(8)Patients with bronchial obstruction or a past history of obstructive pneumonia (but not excluding patients with chronic obstructive pulmonary disease).(9)Patients with primary lung cancer or lung metastasis of a malignant tumor that highly affects the clinical evaluation of pneumonia treatment.(10)Pneumocystis pneumonia (including suspected cases) or active pulmonary tuberculosis (including suspected cases). Patients with eosinophilic pneumonia, interstitial pneumonia, or cystic fibrosis that highly affects the clinical evaluation of pneumonia treatment.(11)Patients who received a systemic antibacterial within 7 days prior to the administration of the study drug (including long-term, low dose macrolide therapy).(12)Respiratory infections caused by pathogens (acid-fast bacilli, fungi, viruses, etc) for which the study drug is not expected to be effective.(13)Patients with active hepatitis B or C virus infection, or HIV infection.(14)Patients who are judged to be unsuitable for participation in this trial by the principal or subinvestigator.

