**Table 1 F1:**
[figure not shown]
Treatment schedule and outcome measures.

In this study, there is no drug or therapy that must be used in combination, but the use of the following drugs during the study period requires caution: formulations that contain aluminum, magnesium, calcium, iron, or zinc; phenylacetic acid- and propionic acid-nonsteroidal antiinflammatory analgesics; rifampicin, phenytoin, or carbamazepine; theophylline or aminophylline hydrate; class IA or III antiarrhythmic drugs; and adrenal corticosteroids (oral agents or injections).

Criteria to discontinue the study are as follows:

•If a patient or their proxy requests to withdraw their consent.•A principal investigator or subinvestigator determines that it is difficult to continue with the study due to illness, etc.•A principal investigator or subinvestigator determines that it is difficult to continue with the study due to adverse events.•If the patient becomes pregnant.•If the patient tests positive for SARS-CoV-2.•A principal investigator or subinvestigator determines that it is difficult to continue with the study for any other reason.

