## 3. Discussion

The efficacy and safety of LSFX for CAP have been shown in clinical trials. NHCAP is pneumonia with a higher risk of resistant bacteria and death compared to CAP. The described study will evaluate the efficacy and safety of LSFX for NHCAP.

LSFX is a quinolone antibiotic that exhibits antibacterial activity against a relatively wide range of bacterial species, including anaerobic bacteria, by inhibiting DNA gyrase and topoisomerase IV.^[3,4]^ Its efficacy and safety against respiratory and otorhinolaryngological infections have been shown in a phase III trial, and it received pharmaceutical approval in September 2019. While the existing quinolone antibiotics strongly inhibit either DNA gyrase or topoisomerase IV, LSFX inhibits both to a similar degree. Thus, it is anticipated to minimize resistant bacteria.^[3,5,6]^ Aspiration is common in NHCAP and pneumonia often recurs, thus, LSFX with a limited risk of resistant bacteria could be a useful option.

LSFX is an oral antibacterial drug and is intended for patients with NHCAP with mild-to-moderate symptoms that could be treated with oral formulations. Though injectable monotherapy is recommended for NHCAP with a risk of resistant bacteria, in actual clinical settings, NHCAP cases that can be treated in an outpatient setting are treated with respiratory quinolones. A risk of resistant bacteria is not necessarily a prognostic factor,^[4]^ and the described study uses a system that allows prompt change in treatment upon appropriately evaluating the condition on Day 3 and 7 of treatment. As such, if a principal investigator or subinvestigator determines it to be appropriate, patients with a risk of resistant bacteria are also allowed to participate.

Based on the evaluation method for NHCAP, according to respiratory infections in the guidelines related to the clinical evaluation methods for antibacterial drugs,^[15]^ the primary endpoint will be set as the TOC. This is the same as the efficacy evaluation for CAP. An early-stage efficacy evaluation will also be set for the secondary endpoints, but these are items recommended as primary endpoints in the Guidance Document for Community-Acquired Bacterial Pneumonia: Developing Drugs for Treatment published by the FDA.^[16,17]^ Thus, evaluation items that could be compared with pneumonia treatment results from overseas will also be included.

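### An antibacterial added for non-responding pneumonia during the LSFX course, and finished by EOT, does not count against 'effective' or 'cured'

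*Protocol article*

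**What the plan says.** The primary endpoint is the TOC rating, 5 to 10 days after EOT (section 2.9.1). The rules that bear on other antibacterials are these.

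- **Before the first dose.** Exclusion 11 (section 2.5) covers "Patients who received a systemic antibacterial within 7 days prior to the administration of the study drug".
- **EOT rating (section 2.8.2).** A patient is effective on the basis of "improvements in 1 or more clinical symptoms accompanied by resolution of fever", together with better images or inflammatory findings. Other antibacterials are not mentioned.
- **TOC rating (section 2.8.3).** The rule opens "Cured satisfies all the following criteria: treatment determined to be effective at the time of EOT; or" and continues "an additional prescription of an antibacterial drug is not necessary after the EOT to the TOC". The next criterion, "body temperature, WBC count, CRP level did not deteriorate after EOT", also starts at EOT. Symptoms and chest X-ray must have improved relative to EOT.
- **TOC indeterminable (section 2.8.3).** An improved patient who received an antibacterial before TOC for something other than NHCAP is indeterminable. This clause has no EOT start.
- **Concomitant drugs (section 2.6, after Table 1).** For a list of drugs, "the use of the following drugs during the study period requires caution". The discontinuation criteria do not name an added antibacterial.
- **Discussion.** "the described study uses a system that allows prompt change in treatment upon appropriately evaluating the condition on Day 3 and 7 of treatment".
- **Analysis sets (section 2.12).** The FAS requires a cured or not cured rating at TOC. The modified FAS adds patients rated at withdrawal. The per protocol set depends on at least 80% adherence to the study drug.

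**The concern.** Cure is meant to measure what LSFX achieves. If a second drug given for the same pneumonia contributed to the recovery, the patient is not evidence of LSFX efficacy. The protocol guards against other antibacterials before the first dose and after EOT. Between the two it guards only against those given for an unrelated reason.

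The asymmetry runs the wrong way. An improved patient treated for an unrelated infection during the course leaves the FAS, while one treated because the pneumonia is not responding can stay in as a success. In a single-arm trial no comparator would offset the error, and its direction is always upward. It reaches the primary endpoint, the EOT secondary endpoint and the lower confidence limit that the primary analysis sets out to obtain.

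**Working it through.** **Step 1. Apply the written rules to each case.**

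| Case | EOT rating (2.8.2) | TOC rating (2.8.3) |
|---|---|---|
| A. Antibacterial during LSFX for another infection; patient improved | Effective possible | Indeterminable, out of the FAS |
| B. Second antibacterial added for the NHCAP, LSFX continued, both finished by EOT | Effective possible | Cured possible |
| C. As B, but the added drug runs past EOT | Effective possible | Unclear; the post-EOT clause is arguably engaged |
| D. LSFX replaced, EOT read as the last LSFX dose | Rated at that dose | New drug falls after EOT: not cured |
| E. LSFX replaced, EOT read as the end of all pneumonia treatment | Effective possible | New drug falls before EOT: cured possible |

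B is the firm gap. D and E both arise because section 2.8.3 counts from the last study-drug dose, while section 2.9.1 ties EOT to the pneumonia.

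**Step 2. Check whether the 'or' matters.** If it is read as 'and', case B still passes, because the patient is effective at EOT and needs nothing afterwards. If it is read literally, case B also passes, and the requirement to be effective at EOT is weakened as well. The gap exists on either reading, and the 'or' conflicts with the demand that all criteria be met.

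**Step 3. Check whether an analysis set would remove case B.** The patient is rated at TOC, so is in the FAS and the modified FAS. LSFX was completed, so the patient is in the per protocol set. The planned sensitivity analysis addresses patients withdrawn before TOC, and this patient was not withdrawn.

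**Step 4. Size, under assumptions.** Inputs from section 2.11: 77 patients, 0.30 indeterminable, cure probability 0.875.

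- Evaluable: 77 × (1 − 0.30) = 53.9, taken as 54. Conversely, 54 / 0.70 = 77.1 reproduces the stated 77. It does so when the precision target is read as a distance of less than 0.10 from 0.875 to a one-sided 95% Clopper–Pearson limit (0.0992 at n = 54, 0.1004 at n = 53). That reading is a separate matter; only the 54 is used here.
- Rated cured: 0.875 × 54 = 47.25, taken as 47.
- Let k of the 47 be case B patients, re-rated not cured. The rate is (47 − k)/54. The lower limit is the 0.025 quantile of Beta(47 − k, 54 − 47 + k + 1), the two-sided 95% Clopper–Pearson limit.

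| k | Cure rate | Lower limit |
|---|---|---|
| 0 | 47/54 = 87.0% | 75.1% |
| 1 | 46/54 = 85.2% | 72.9% |
| 2 | 45/54 = 83.3% | 70.7% |
| 3 | 44/54 = 81.5% | 68.6% |
| 5 | 42/54 = 77.8% | 64.4% |

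Each such patient moves the rate by 1/54 = 1.9 points and the lower limit by about 2.1 to 2.2 points.

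**The case against.** The strongest reply is that the intended meaning is visible. By singling out antibacterials given for other reasons, section 2.8.3 suggests that one given for the NHCAP was meant as failure. The change of treatment in the Discussion reads most naturally as a switch, which the rule catches if EOT is the last LSFX dose. What remains is a narrow route: LSFX kept, a drug added, both finished by EOT, and symptoms and X-ray still improving to TOC. Nothing in the article describes add-on therapy, and the full protocol may forbid it.

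Much of this stands, and it limits the point. It does not close the gap, because the intended meaning is not written in the criteria. A ban elsewhere would not say how a patient who received an added drug is rated. The endpoint definitions are given here in full sentences with their own antibacterial clauses, so the fault lies in a stated window, not in condensation.

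A reader might infer more than the document supports:

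- *That no outcome rule mentions antibacterials before EOT.* The indeterminable clause does.
- *That every rescued patient becomes a success.* A switch is probably caught, and case C is open.
- *That the caution list permits rifampicin as rescue.* It stands there beside phenytoin and carbamazepine; nothing presents it as pneumonia treatment.
- *That patients at risk of resistant bacteria are most affected.* No figure supports this, and the Discussion says that this risk does not necessarily determine prognosis.
- *That the Day 3 rating is biased in the same way.* The Discussion places changes of treatment upon that evaluation, so they would normally follow it.

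**Conclusion.** The point holds for an antibacterial added for the NHCAP and completed within the LSFX course: the written criteria allow *effective* and *cured*, and no planned analysis would remove or reveal the patient. For a replacement of LSFX, the rating depends on which meaning of EOT applies, and sections 2.8.3 and 2.9.1 need to be aligned.

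The bias is upward, about 1.9 points on the cure rate per affected patient. This assumes 54 evaluable patients; the lower limits above also assume 47 rated cured. The number affected is unknown and may be zero, so the table shows sensitivity and is not an estimate. The point warrants correction because it sits in the primary endpoint, runs in one direction and costs little to close.

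**What to change.** Change the classification rules only; treatment decisions stay with the physicians.

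1. In sections 2.8.2 and 2.8.3, start the antibacterial criterion at the first LSFX dose. Any non-study systemic antibacterial given for insufficient response of the NHCAP between first dose and the assessment rates the patient ineffective at EOT and not cured at TOC.
2. Define EOT as the last LSFX dose, and use that definition in section 2.9.1 as well.
3. State separately how a patient is rated when LSFX is substituted for intolerance. That is a different event from non-response and should not be decided by default.
4. Replace the 'or' in the cure rule so that it agrees with the requirement that all criteria be met.

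The cost is a wording change and the recording of date and indication for any added antibacterial. The reported cure rate may be slightly lower.

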### 2.4. Inclusion criteria

Patients should meet the following criteria to be enrolled:

(1)Patients who are older than 20 at the time of providing informed consent.(2)Patients who present acute manifestation of obvious infiltrates in a chest X-ray or high-resolution computed tomography image obtained within 48 hours of administration of the study drug.(3)Patients who meet both 1) and 2):1)Patients who have at least one of the following symptoms:a.Cough.b.Purulent sputum or sputum with increased purulence.c.Abnormal findings in auscultation or percussion (moist rales, dullness to percussion, decreased breathing sounds, etc).d.Worsening of either or both dyspnea and tachypnea.e.Fever: ≥ 37°C (axillary temperature).
2)Patients who have at least one of the following:a.Increased C-reactive protein (CRP) level.b.Increased white blood cell count (> 10,000/ mm^3^), or stab cells > 15%.c.Hypoxemia (PaO_2_ < 60 Torr or SpO_2_ < 90%).

(4)Patients who are classified as mild or moderate by the A-DROP scoring system.^[12]^(5)Patients who meet at least one of the following:1)Admittance to a long-term care or nursing home.2)Discharge from hospital in the preceding 90 days.3)Elderly or physically disabled people who require care.4)Outpatients who regularly receive infusion therapy (including dialysis, antibiotics, anticancer agents, immunosuppressant drugs, etc.) or hemodialysis.
(6)Patients who are able to take drugs orally.(7)Written informed consent has been provided by the patient or legally acceptable representative to participate in the study.

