### 2.9. Study endpoints

#### 2.9.1. Primary endpoint.

The primary endpoint is the efficacy evaluation at the time of TOC (5–10 days after the EOT for pneumonia).

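### Entry accepts an infiltrate seen only on HRCT, but the cure rule demands an improved chest X-ray, so such a patient cannot be scored cured as written; how many are affected is unknown

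*Protocol article*

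**What the plan says.** All references are to the protocol article.

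- **Entry (2.4, criterion 2).** The patient must show "obvious infiltrates in a chest X-ray or high-resolution computed tomography image obtained within 48 hours of administration of the study drug". Either modality is enough.
- **Day 3 and end of treatment, EOT (2.8.1, 2.8.2).** Part of the definition of an effective result is that "there will be improvements to pneumonia images or inflammatory findings". No modality is named, and imaging is an alternative to the inflammatory findings.
- **Cure at TOC (2.8.3).** The list opens with "Cured satisfies all the following criteria" and ends with "improved symptoms compared to the EOT; and improved chest X-ray compared to the EOT". One modality is named, improvement is required, and no alternative is offered.
- **Third category (2.8.3).** A patient may instead be "indeterminable (lack of evaluation information, evaluation items worsening due to causes other than pneumonia", with a further reason concerning antibacterials given for something other than NHCAP.
- **Use (2.9.1, 2.12).** "The primary endpoint is the efficacy evaluation at the time of TOC". The full analysis set (FAS) holds only patients who can be rated cured or not cured at TOC. The primary analysis gives a 95% Clopper–Pearson interval, with interest in its lower limit.

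**The concern.** The entry criterion and the primary endpoint use different imaging standards. A patient can enter because HRCT showed an infiltrate that the plain film did not. For that patient the film has no finding to improve on, at EOT or at TOC, however complete the recovery. If every listed criterion must hold, cure is out of reach from the day of entry.

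Two scores remain, and the text does not choose between them. Not cured counts a recovered patient as a failure and lowers the cure rate. Indeterminable, for lack of evaluation information, takes the patient out of the FAS. Neither describes the response to the drug. The trial has a single arm, so no control group shares the distortion, and the result will be read as an absolute rate. The sensitivity analysis in 2.12 does not help: the modified FAS adds patients who can be rated at withdrawal and leaves the cure rule unchanged.

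**Working it through.** **1. Does the conflict follow from the text?**

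| Visit | Modality accepted | Role of imaging |
|---|---|---|
| Entry (2.4) | chest X-ray or HRCT | required, either one |
| Day 3, EOT (2.8.1, 2.8.2) | not specified | alternative to inflammatory findings |
| TOC (2.8.3) | chest X-ray only | required for cure |

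Take a patient with an HRCT infiltrate and a clear film at entry. Criterion 2 of 2.4 is met. An effective rating at EOT is possible through the inflammatory findings. At TOC the film cannot be better than a film that was already clear, so the last component fails and cure is not available. No outside fact is needed.

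The list in 2.8.3 contains an *or* after its first item. It joins the clause on EOT efficacy to the clause on further antibacterials. The X-ray clause is attached at the end by *and*, so the *or* does not bypass it.

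**2. How large could the effect be?**

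Inputs from the documents: target 77 patients and an indeterminable share of 0.30 (2.11), so 77 × 0.70 = 53.9, taken as 54 evaluable. Assumed cure probability 0.875 (2.11), so 54 × 0.875 = 47.25, taken as 47 cured.

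Input not in the documents: the share *s* of evaluable patients whose infiltrate shows only on HRCT. I assume 0 to 30%.

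Worst case: all HRCT-only patients are scored not cured, and cure would otherwise be equally likely in both groups. Cured *x* = 47 × (1 − *s*), rounded. The lower 95% limit is Clopper–Pearson, the 0.025 quantile of Beta(*x*, 54 − *x* + 1).

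| *s* | 47 × (1 − *s*) | Cured / 54 | Rate | Lower 95% limit |
|---|---|---|---|---|
| 0% | 47.0 | 47 | 0.870 | 0.751 |
| 5% | 44.65 | 45 | 0.833 | 0.707 |
| 10% | 42.3 | 42 | 0.778 | 0.644 |
| 20% | 37.6 | 38 | 0.704 | 0.564 |
| 30% | 32.9 | 33 | 0.611 | 0.469 |

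Rounding matters slightly. Starting from 0.875 × 0.90 × 54 = 42.5 and rounding up gives 43/54 = 0.796 (lower limit 0.665) at 10%.

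**3. If they are scored indeterminable instead**

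They leave the FAS, and under the assumption above the expected cure rate among those who remain is unchanged. The cost is precision. The 54 already stands after a 30% allowance for indeterminable patients, which is 77 − 54 = 23 patients. HRCT-only patients scored this way may be part of those 23, so subtracting them from 54 again could count them twice. The evaluable number falls below 54 only if indeterminable patients from all causes exceed the allowance.

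**The case against.** **The size of the group is unknown.** Entry on HRCT does not mean that the X-ray was negative; many patients may have had both, with the infiltrate on each. Criterion 2 also asks for "acute manifestation of obvious infiltrates in a chest X-ray or high-resolution computed tomography image", which makes subtle findings less likely. The group may be small or empty. This stands. A reader might infer from the table that the primary cure rate is materially biased, but the documents give no HRCT-only share, so they do not support that. The 0% row, with no effect, is as compatible with them as any other.

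**The full protocol may settle it.** The article condenses version 4.0, and the content of Table 1 is not visible here; imaging instructions may sit there. This stands in part. A reader might infer that the 24 hospitals will each improvise a rule, and that cannot be shown from the article. But a schedule of which image is taken when would not alter a cure definition that asks for X-ray improvement.

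**The problem is wider than modality.** Since improvement is measured against EOT, a patient who entered with an X-ray infiltrate but whose film had cleared by EOT also cannot improve further. This stands, and it bears on the repair: a fix confined to HRCT-only patients would leave these patients unable to be cured and would create two cure standards in one primary endpoint.

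**Some would not be cured anyway.** A patient whose treatment was not effective at EOT fails regardless of imaging. True; the misclassification concerns only patients who otherwise meet the cure criteria, and the table applies it only to the 47.

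**Conclusion.** The point holds as a conflict between the entry criterion and the primary endpoint. Under 2.4 a patient can be eligible on HRCT alone; under 2.8.3 that patient cannot be scored cured on the literal reading if the infiltrate never showed on X-ray. The consequence is a downward bias in the cure rate or a loss from the FAS, and the text does not say which.

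The size is not established. The worst case runs from no effect at a 0% share, through a drop of 0.037 in the cure rate at 5% (0.870 − 0.833), to a drop of 0.259 at 30% (0.870 − 0.611). These figures rest on 54 evaluable patients, 47 otherwise cured, the same underlying cure rate in both groups, and every HRCT-only patient scored not cured. A reader might also infer a certain fall in evaluable patients to about 49, 43 or 38 at shares of 10%, 20% and 30%. That does not follow, because the 30% allowance in 2.11 may already cover them.

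The case for acting is that a stated rule for the primary endpoint misclassifies a kind of patient the trial chose to admit, and that the correction is cheap.

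**What to change.** In 2.8.3, replace the X-ray component with one imaging criterion that applies to every patient and can be met whatever the entry modality, using the modality-neutral term of 2.8.1 and 2.8.2. For example: *pneumonia images improved from baseline, or, where no infiltrate is visible on chest X-ray at baseline or at EOT, no new or worsened infiltrate on chest X-ray at TOC.* No repeat HRCT is required. The second limb also covers a film already clear at EOT, so one sentence repairs both situations.

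Record in the EDC whether the entry infiltrate was seen on chest X-ray, on HRCT or on both, and report the cure rate by entry modality.

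Cost: one sentence, one EDC field and one descriptive table; no added imaging. The downside is a somewhat less demanding imaging component for patients with no visible X-ray infiltrate, so their number should be shown. The example also moves the reference for the first limb from EOT to baseline, which should be a deliberate choice and stated as such.
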